### Data entry and quality control

Study data will be managed using the SecuTrial *Electronic Data Capture* system, hosted by the IT Department of the University Hospital Basel. The system automatically validates entered data for completeness and detects discrepancies. An audit trail records all entries and modifications, including reasons for changes, timestamps and user identification. Monitoring visits will be conducted regularly at the investigator’s site throughout the study. Source documents will be made available to monitors, and any queries will be addressed to ensure data accuracy and adherence to study protocols.

### Primary objective and outcome

The primary objective of this study is to assess the effects of intranasal OXT compared with placebo on anxiety levels and emotion recognition in patients with AVP-D. Clinically relevant improvement is defined as either:

A decrease in the STAI-T Score by ≥5 points (range: 20–80)^12^An increase in EmBody/EmFace Task performance by ≥4 points (range: 0–42).^14^

The primary analysis will compare success rates—defined as achieving clinically meaningful improvement in anxiety or emotion recognition—between the OXT and placebo groups.

We hypothesise that the OXT group will exhibit a higher success rate than the placebo group. Additional details are provided in the online supplemental material.

*State-Trait Anxiety Inventory (STAI):* The STAI questionnaire evaluates anxiety through 40 items scored from 1 (‘almost never’) to 4 (‘almost always’), with total scores ranging from 20 to 80. It includes two subscales:

STAI-S: Measures current anxiety (‘right now’), focusing on feelings such as nervousness or arousal.STAI-T: Assesses general anxiety tendencies or ‘anxiety proneness’.

A score above 39 indicates clinically significant anxiety. STAI-T will be evaluated on days 0 and 28, while STAI-S will be assessed on days 0, 14 (before and during TSST and fMRI) and 28.

*EmBody/EmFace tasks*: These tasks measure the recognition of emotions (angry, happy, neutral) in body and facial expressions through 42 standardised stimuli, each lasting 1.5 s. Participants select the perceived emotion in a three-option forced-choice format. Scores range from 0 to 42, with higher scores indicating improved recognition. Task design minimises biases (eg, ethnicity or clothing cues) and avoids consecutive repeats of the same actor, emotion or viewpoint. Each task takes approximately 5 min and will be conducted on days 0, 1 and 28.

### Secondary objectives

The three main secondary objectives are to determine whether OXT, as compared with placebo, has favourable effects on:

Emotion recognition and empathyCorrect recognition of facial expressions assessed on the Facial Emotional Recognition Task (FERT)Levels in cognitive and emotional empathy assessed on the Multifaceted Empathy Task (MET)Hormonal and subjective response to psychological stress (assessed on day 14 in a subset of patients, social-stress substudy)Change in cortisol levels assessed on the Trier Social Stress Test (TSST)Change in anxiety levels using the STAI (State-Anxiety Scale, STAI-S) on the TSSTAmygdala and subjective response in the functional MRI scan (assessed on day 14 in a subset of patients, fMRI substudy)Amygdala response to the Emotional Face Matching Task (EFMT)Change in acute anxiety levels using the STAI-S on the EFMT.

We hypothesise that intranasal OXT compared with placebo will, first, improve empathy and emotion recognition, second, reduce cortisol and acute anxiety levels in response to psychological stress, and third, reduce amygdala reactivity and acute anxiety levels in response to fearful faces.

Further objectives are to investigate whether the intervention as compared with placebo has effects on:

Other psychological measures (assessed on day 0 and reassessed on day 28):Change in anxiety using the Hamilton Anxiety Rating ScaleChange in alexithymia using TAS-20Change in autistic traits using the Autism-Spectrum Quotient Test (AQ)Change in mood using the Beck Depression Inventory (BDI-II)Change in QoL using the Posterior Pituitary QoL Questionnaire (PP-QoL) and the Patient-Reported Outcomes Measurement Information System (PROMIS)Change in sexual desire (Sexual Desire Inventory-2, SDI-2) and in sexual behaviour (Sexual Behaviour Questionnaire, SBQ-G)Change in eating behaviour using the Three-Factor Eating Questionnaire – Revised 18 item (TFEQ-T18)Metabolic parameters (assessed on day 0 and re-assessed on day 28):Change in weightChange in HbA1c, glucose, insulin, C-peptide, lipid profile, IL-6, CRP (C-reactive protein), cortisolChange in satiety and satiation by using numerical rating scalesObjective assessment of a third person (assessed on day 0 and reassessed on day 28):Change in the objective assessment of a close third person regarding socioemotional characteristics using a predefined 20-item statement list with numerical analogue scalesSafety measure (assessed on day 0 and reassessed on day 14 and day 28):Occurrence of hyponatraemia.

### Study procedure

See figure 2 and fiugre S1(online supplemental figure 1) for the study procedure.

*Baseline evaluation* (day 0, without IMP): Participants will complete the STAI-T, Hamilton Anxiety Inventory and TAS-20 questionnaires and perform computerised emotion recognition/empathy tasks (EmBody/EmFace, FERT, MET). Blood and urine samples will be collected for baseline analysis of hormones and metabolic markers. Participants will conduct self-reported questionnaires (STAI-S, BDI-II, AQ, PP-QoL, PROMIS), followed by an ad libitum meal to assess satiation. Close third-person assessments and questionnaires on sexual desire, behaviour (SDI-2, SBQ-G) and eating behaviour (TFEQ-18) may also be completed.

*Main visit 1* (day 1, with IMP): Participants will administer their first dose of intranasal OXT/placebo under supervision. Computerised tasks and additional questionnaires (STAI-S, subjective effects scales) will be completed at peak OXT concentration. Blood samples will be collected, and a second ad libitum meal will be provided to assess physiological and behavioural responses.

*Main visit 2* (day 28±2, with IMP): Primary outcomes (STAI-T and EmBody/EmFace tasks) will be completed. Participants will undergo final assessments, including blood sampling, IMP diary reviews, adverse event documentation and standardised questionnaires (eg, AQ, BDI-II, PP-QoL).

#### Optional substudies (day 14±2)

Social stress (TSST): Participants will perform stress-inducing tasks under the supervision of a panel to assess cortisol and anxiety responses.fMRI: Participants will undergo a functional MRI using photographs from a validated set of facial stimuli that activate the amygdala and allowing isolation of amygdala reactivity to each emotional expression. Imaging will assess brain activity (resting state, EFMT) and structure. Blood samples and subjective questionnaires will complement the imaging data.

#### Concomitant desmopressin treatment

Hyponatraemia is a common complication of desmopressin therapy in AVP-D, affecting up to 27% of outpatients. To mitigate this risk, all participants will be instructed to use the ‘desmopressin escape method’, allowing breakthrough aquaresis before the next dose, which has been shown to significantly reduce hyponatraemia compared with rigid dosing. The OXT dose will remain stable throughout the study, while desmopressin dosing may be adjusted if needed; patients will be educated on symptoms of hyponatraemia, and daily desmopressin dose and fluid intake will be documented in a diary.

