#### Modification, preventive measures and concomitant treatments

No dose modification is intended. No rescue medication for the trial participants is foreseen. In case of necessity of additional treatments during the intervention period, the participants will be instructed to document this in the drug-diary and inform the investigators accordingly. No concomitant care beyond the intervention is planned. Patients must be on stable hormone replacement therapy with desmopressin and, in case of additional anterior pituitary deficiencies, with the respective substitution therapies for at least 3 months before participation. If a change in replacement therapy is needed, each case will be discussed with the study team, and a possible change will preferably be planned before inclusion in the trial and there will be a wait of 3 months for stability. Concomitant psychotherapy (eg, medical therapy with psychotropics, behavioural therapy) is only allowed if this is established for at least 3 months before study inclusion and no discontinuation is planned during the intervention.

The first dose of the study medication will be given the day after successful inclusion. After that, study medication will be administered by the patient in the morning and afternoon daily at home. The empty carton containers with the eight sprays of the study medication must be returned to the investigator for compliance control at the follow-up visit on day 28 (±2). In addition, patients will be given a drug diary to document their use of IMP (Investigational Medicinal Product) and desmopressin.

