#### *Safety visit* (day 14±3)

Participants not involved in substudies will undergo sodium level monitoring either at the study site or by their healthcare provider. Plasma sodium will be assessed on day 14 and day 28 at the study site. If the patients are travelling from further distances, this control can be performed by their general practitioner or endocrinologist. Procedure if hyponatraemia occurs during the study:

Mild hyponatraemia (plasma sodium 130–134 mmol/L): The patient will again be instructed in detail by our investigator on how to perform the ‘Desmopressin Escape’ method. We will follow-up on plasma sodium within the next 7 days.Moderate hyponatraemia (plasma sodium 125–130 mmol/L): Procedure see above. However, plasma sodium control is done earlier, after 2–3 days.Severe hyponatraemia (plasma sodium <125 mmol/L): The patients are monitored in the hospital until normalisation of the sodium value/symptomatic improvement after detailed assessment by the investigator.

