#### Planned analyses

Full analysis set (FAS): All randomised participants analysed as per intention-to-treat.Per-protocol set: Includes patients with psychological baseline assessments on day 0, primary outcome data on day 28 and ≥50% medication adherence.

The primary analysis will compare success rates between groups using Fisher’s exact test (α=0.05) on the FAS. Changes in STAI-T and EmBody/EmFace Task scores will be analysed using linear regression models, adjusting for baseline values. Results will include mean differences with 95% CIs. Secondary outcomes will be analysed using linear mixed-effects models for repeated measures, focusing on estimating OXT effects with 95% CIs. Adjustments for multiple testing will use the Bonferroni-Holm procedure. Descriptive statistics will summarise the outcomes for each treatment group.

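### The printed hyponatraemia procedure specifies no action on the blinded spray at any grade, including sodium below 125 mmol/L, and the oxytocin dose is fixed without a safety exception

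*Protocol article*

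**What the plan says.** Two sections of the protocol article fix the dose of the study drug. Under Modification, preventive measures and concomitant treatments: "No dose modification is intended". Under Concomitant desmopressin treatment: "The OXT dose will remain stable throughout the study, while desmopressin dosing may be adjusted if needed". Neither sentence is qualified for safety.

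The Safety visit section sets out what to do when sodium is low:

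- **Mild (130–134 mmol/L):** "The patient will again be instructed in detail by our investigator on how to perform the" desmopressin escape method, with a repeat sodium within 7 days.
- **Moderate (125–130 mmol/L):** as for mild, but "However, plasma sodium control is done earlier, after 2–3 days".
- **Severe (below 125 mmol/L):** "The patients are monitored in the hospital until normalisation of the sodium value/symptomatic improvement after detailed assessment by the investigator".

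Three other places bear on the point. The Discussion says that oxytocin acts at V2 receptors with lower affinity than vasopressin, that synergy is possible, and that less desmopressin may be needed. Interim analyses makes an excess of five or more severe cases in the oxytocin group the prespecified signal for the safety board. Study procedure describes the last main visit as "day 28±2, with IMP): Primary outcomes (STAI-T and EmBody/EmFace tasks) will be completed".

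**The concern.** The trial adds a drug with a possible antidiuretic effect to desmopressin, in patients who are already prone to hyponatraemia. The sponsor recognises this and prints a procedure for individual patients. In that procedure desmopressin is the only drug acted on. The blinded spray, which may be the added contributor, is not mentioned at any grade, and the dose statements elsewhere say that it does not change.

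A site physician who faces a sodium below 125 mmol/L therefore has a written instruction to admit and monitor, and none about the next dose of spray. Investigators are blinded, so they cannot settle the matter by knowing the arm. Two centres are active and two more are planned, so handling could differ between sites. At stake are participant safety and uniform conduct, not the primary test.

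**Working it through.** This is mainly a comparison of texts. The plan gives no figure to reproduce on this point.

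**Step 1: the rules side by side**

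| Situation | Desmopressin | Sodium and care | Study spray |
|---|---|---|---|
| General rule | May be adjusted | Checked on days 14 and 28 | Dose stable, no modification intended |
| 130–134 mmol/L | Escape method re-taught | Recheck within 7 days | Not mentioned |
| 125–130 mmol/L | As above | Recheck after 2–3 days | Not mentioned |
| Below 125 mmol/L | Not mentioned | Hospital monitoring, investigator assessment | Not mentioned |

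The last column holds only the general rule, and no grade overrides it.

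**Step 2: does another printed rule fill the gap?** The safety board rule does not. It is triggered by a difference of at least five severe cases between arms, its review follows completion of treatment by 60% of participants (0.60 × 112 = 67.2, so about 67), and it leads to a recommendation for the trial. It does not guide the care of one patient.

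**Step 3: what would a hold cost in adherence?** The per-protocol set requires "primary outcome data on day 28 and ≥50% medication adherence". Assume that adherence means doses taken divided by doses scheduled, with no other missed doses. Dosing is twice daily, and the course lasts 28 (±2) days.

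Share taken = 2 × (course days − hold days) / (2 × course days)

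| Hold | 28-day course (56 doses) | 26-day course (52 doses) |
|---|---|---|
| 3 days | 50/56 = 89.3% | 46/52 = 88.5% |
| 7 days | 42/56 = 75.0% | 38/52 = 73.1% |
| 14 days | 28/56 = 50.0% | 24/52 = 46.2% |

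Short holds keep a participant well above the threshold. A 14-day hold just meets it on the nominal course and misses it on the shortest permitted one.

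**The case against.** The strongest reply is that this is a condensed article. Criteria for interrupting or stopping treatment in a participant are usually in the full protocol (V.5.0), which is not shown. The fixed-dose sentences can also be read as ruling out titration rather than interruption. The article supports that reading: after a confirmed pregnancy further participation is not allowed, so treatment ends although neither dose statement mentions an exception. Severe cases are managed in hospital after detailed investigator assessment, and participants may withdraw at any time. Acting first through desmopressin is reasonable, given oxytocin's lower V2 affinity and the sponsor's view that synergy may reduce the desmopressin dose needed.

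Much of this stands. A reader might infer that the protocol orders the spray to continue at sodium below 125 mmol/L, or forbids stopping it. The document says neither. For the same reason, counting the doses left after a severe value does not measure harm, because the count presupposes continuation that nothing printed requires.

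The reply does not remove the point. The article does not leave the topic to the full protocol: it prints all three grades and states the dose rule twice. What it prints is specific about desmopressin, sodium checks and admission, and silent on the spray.

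**Conclusion.** The point holds in a limited form: as printed, the oxytocin dose is fixed without a safety exception, and no grade of the hyponatraemia procedure specifies an action on the blinded spray. Discretion remains, and the full protocol may already contain a rule. If it does, the article's wording only needs to be aligned with it.

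The size cannot be put as a number of patients. The document gives no rate of severe hyponatraemia. Its figure of up to 27% of outpatients relates to desmopressin treatment and is not split by grade. The sample size, the primary test and membership of the full analysis set do not change. It is a worthwhile safety clarification at low cost.

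The adherence figures rest on the assumed definition of adherence. A reader might take from the 28-day column that any hold of up to 14 days is safe for the per-protocol set. The permitted 26-day course shows that it is not.

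**What to change.** In the Safety visit procedure, state that the spray is withheld, without unblinding, at sodium below 125 mmol/L or with symptomatic hyponatraemia, pending investigator assessment. The rule applies to either arm, so the allocation need not be known. Make the two fixed-dose statements, under Modification and under Concomitant desmopressin treatment, subject to this exception. Because the last main visit is described as taking place with the study drug, add that a participant still on hold completes the STAI-T and EmBody/EmFace tasks without the spray.

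The cost is a few lines in an amendment, or only a wording change if the full protocol already has the rule. The downside is that a few participants may be off drug at day 28, and long holds may take some out of the per-protocol set. With 56 per group, each participant whose result changed from success to failure would move that arm's success rate by 1/56 = 1.8 percentage points, against a planned difference of 25 points.

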#### *Safety visit* (day 14±3)

Participants not involved in substudies will undergo sodium level monitoring either at the study site or by their healthcare provider. Plasma sodium will be assessed on day 14 and day 28 at the study site. If the patients are travelling from further distances, this control can be performed by their general practitioner or endocrinologist. Procedure if hyponatraemia occurs during the study:

Mild hyponatraemia (plasma sodium 130–134 mmol/L): The patient will again be instructed in detail by our investigator on how to perform the ‘Desmopressin Escape’ method. We will follow-up on plasma sodium within the next 7 days.Moderate hyponatraemia (plasma sodium 125–130 mmol/L): Procedure see above. However, plasma sodium control is done earlier, after 2–3 days.Severe hyponatraemia (plasma sodium <125 mmol/L): The patients are monitored in the hospital until normalisation of the sodium value/symptomatic improvement after detailed assessment by the investigator.

### Sample size calculations and statistical analyses

The study will compare the success rates (SR) between the OXT and placebo groups. We hypothesise that the success rate is higher in the OXT group than in the placebo group. The null hypothesis is that the difference in the success rates between OXT and placebo (success rate difference (SRD)) is zero (H0: p_placebo=p_OXT, hence SRD=0).

For sample size estimation we used a simulation approach. We assumed a success rate of 10% under placebo and explored the sensitivity of the sample size to the expected success rate under OXT ranging from 20% to 50% (effect size θ=SRD 0.1–0.4). For each effect size θ and sample size N under consideration, we sampled 999 times from two binomial distributions with N/2 each and p placebo=0.1, and p OXT=0.1 + θ. The two proportions were then tested for a difference from zero (H0: SRD=0) using Fisher’s exact χ^2^-test at a significance level of α=0.05, using the chisq.test() function in R without continuity correction. The sample size is estimated to reject the null hypothesis with a statistical power of at least 85%.

For intranasal OXT, we expect a moderate effect, and a moderate effect size would also be regarded as clinically relevant. For binary outcomes, the effect size can be expressed as the SRD, that is, success rate under treatment minus success rate under control. The inverse of the SRD is the number needed to treat (NNT) which has a more clinically practical meaning. For example, a moderate SRD of 20% corresponds to an NNT of five patients. This means that five patients are needed to be treated in order to observe one patient with success. The sample size required depends on the true SRD θ. For an expected SR of 10% under placebo and 35% under OXT (SRD 0.25), a total of 112 patients (56 patients per group) should be recruited in order to end up with a total of 94 evaluable patients, considering a dropout rate of 15%.

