## Methods

### Study design

This is a randomised, double-blind, placebo-controlled, parallel-arm trial investigating the effects of intranasal OXT compared with placebo in patients with AVP-D (figure 1). The trial includes a 28-day treatment period, with patients randomised to receive either intranasal OXT (24 IU twice daily) or placebo. Participants will attend study visits on screening/day 0, day 1 and day 28 (±2). Optional substudies at day 14 will include fMRI (functional Magnetic Resonance Imaging) assessments and social-stress testing.

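### The 10% placebo success rate is not derived from the either/or endpoint and is probably too low; power for a 25-point difference is shown at no other placebo rate

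*Protocol article*

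**What the plan says.** Under Sample size calculations and statistical analyses the protocol article states: "We assumed a success rate of 10% under placebo". The oxytocin rate is explored from 20% to 50%; the placebo rate is held fixed. The chosen scenario is 10% vs 35%, a success rate difference (SRD) of 0.25, with at least 85% power, 94 evaluable patients and 112 recruited at 15% dropout. The simulation tested each sample "at a significance level of α=0.05", "using the chisq.test() function in R without continuity correction". Under Planned analyses, however: "The primary analysis will compare success rates between groups using Fisher’s exact test (α=0.05) on the FAS".

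Under Primary objective and outcome a patient succeeds on either a STAI-T fall of at least 5 points or this: "An increase in EmBody/EmFace Task performance by ≥4 points". The task has 42 stimuli. "Participants select the perceived emotion in a three-option forced-choice format". It is given on days 0, 1 and 28.

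Table 1 admits patients with STAI-T of at least 39 or TAS-20 of at least 52. Under Study design: "Participants will attend study visits on screening/day 0, day 1 and day 28". The qualifying STAI-T may therefore also be the baseline value.

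**The concern.** An either/or rule adds two routes to success, and each can be met without any real change. A score out of 42 varies between visits by chance, and repeating the task may add practice. STAI-T varies too, and patients who entered because of a high STAI-T will tend to fall back at retest. The placebo rate is the input that these features push up, and it is the one input that the sensitivity analysis leaves alone.

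For a fixed SRD, a placebo rate that moves from 10% towards the middle of the scale raises the variance of the difference and lowers power. A true 25-point benefit could then be missed more often than the plan states, in a rare disease where a second trial would be hard to mount. The type I error is not affected.

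**Working it through.** **1. The plan's own figure.** Inputs from the sample-size section: 10% vs 35%, α = 0.05 two-sided, 47 per group. Power = Σ Σ Bin(x; 47, 0.10) · Bin(y; 47, 0.35) over all outcomes (x, y) that the test rejects.
- Uncorrected chi-square: 85.4% (46 per group gives 84.5%), so 94 evaluable patients reproduces.
- 94 / 0.85 = 110.6, so 111, or 112 for equal groups. This also reproduces.
- Fisher's exact test, same inputs: 78.6%.

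The arithmetic is sound for the test that was simulated. The question is the 10%.

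**2. Chance gains on the task.** Assumed model: two independent Binomial(42, p) scores, no true change, accuracy p not given in the article. The unequal-item column draws item probabilities from a Beta distribution with the same mean and concentration 3.

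| Assumed accuracy | P(gain ≥ 4), equal items | P(gain ≥ 4), moderately unequal items |
|---|---|---|
| 70% | 20.2% | – |
| 75% | 18.8% | 15% |
| 80% | 16.9% | 13% |
| 85% | 14.1% | 11% |
| 90% | 9.9% | 7% |
| 93% | 6.5% | – |
| 95% | 3.9% | – |

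Very unequal items (concentration 2) give 9.5% at 85% accuracy and 5.9% at 90%. Practice would raise all of these.

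**3. Spontaneous STAI-T falls.** Assumed, not in the article: SD 8–12, retest correlation r of 0.8–0.9, no mean change. SD of change = SD·√(2(1 − r)); P(fall ≥ 5) = Φ(−4.5 / SD of change), with a half-point continuity correction.
- SD 8, r = 0.9: 8 × √0.2 = 3.58, giving Φ(−1.26) = 10%.
- SD 12, r = 0.8: 12 × √0.4 = 7.59, giving Φ(−0.59) = 28%.

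**4. Composite.** If the components are independent, the rate is 1 − (1 − a)(1 − b), with task rate a and STAI-T rate b.
- Low end: 1 − 0.93 × 0.90 = 16%.
- High end: 1 − 0.80 × 0.72 = 42%.

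In reverse, a 10% composite needs b = 1 − 0.90 / (1 − a):
- a = 9.9% (90% accuracy, equal items): b about 0%.
- a = 6.5% (93%): b at most 3.7%.
- a = 3.9% (95%): b at most 6.3%.
- 85% accuracy or lower, equal items: the task alone already exceeds 10%.

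**5. Power for SRD 0.25 by placebo rate** (exact enumeration, chi-square / Fisher).

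| Placebo vs oxytocin | 47 per group | 56 per group |
|---|---|---|
| 10% vs 35% | 85.4% / 78.6% | 91.1% / 86.4% |
| 15% vs 40% | 79.3% / 72.4% | 85.9% / 80.8% |
| 20% vs 45% | 75.1% / 68.0% | 82.3% / 76.8% |
| 30% vs 55% | 69.2% / 61.5% | 76.3% / 70.1% |
| 40% vs 65% | 68.7% / 60.9% | 75.5% / 69.1% |

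**The case against.** A reader might infer that 10% is incompatible with the endpoint and that 85% power cannot be reached. The documents do not support that. They give no task accuracy, SD or retest correlation, and at 93–95% accuracy with few STAI-T responders a composite near 10% is possible. That case has a cost of its own: under the binomial model 66% of patients at 93% accuracy and 84% at 95% would start at 39 or more and could not gain 4 points, so the assumed 35% under oxytocin would have to come almost wholly from STAI-T.

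Four further objections stand in part.
- Entry is by STAI-T or TAS-20. For patients admitted on TAS-20 alone, selection does not push the STAI-T baseline upward, so regression to the mean affects only part of the sample.
- About 7 points of any gap between 85% and a Fisher figure (85.4% − 78.6% = 6.8) come from simulating one test and planning another. That is a separate matter, so like-for-like comparisons should use the chi-square column.
- The primary analysis is on all randomised patients. If all 56 per group contribute at the same rates, the loss is smaller, as the right-hand column shows.
- A null primary result would not stand alone, because baseline-adjusted regressions of both scores with 95% CIs are planned.

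The full protocol and the supplement may justify the 10%; neither is shown. The article nevertheless states the input, the range explored and the resulting size, and varies only one of the two rates.

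**Conclusion.** The concern holds in a limited form. The 10% is an unsupported input and probably too low for this endpoint; it is not shown to be impossible. The claimed 85% applies to one scenario: 10% vs 35%, uncorrected chi-square, 47 per group. If the placebo rate is 20–30% and the difference is still 25 points, power at 47 per group is about 69–75% by chi-square and 62–68% by Fisher. With all 56 per group analysed it is 76–82% and 70–77%.

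The power figures are exact, given the rates. The judgement that the placebo rate exceeds 10% rests on the binomial model for the task, on the assumed STAI-T SD and retest correlation, and on independence of the components.

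**What to change.** In the sample-size section:
- Derive the placebo rate from the two components, stating the expected task accuracy and the SD and retest correlation of STAI-T, with their sources.
- Show power for SRD 0.25 over placebo rates of 10–40%, using the test named under Planned analyses.
- Restate the claimed power accordingly. Enrolment need not change.

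Optionally, tabulate the blinded pooled success rate when data are cut at 60% for the DSMB and compare it with the implied (10% + 35%) / 2 = 22.5%. This is supportive only. A pooled rate cannot separate the placebo rate from the treatment effect: 20% vs 25% also pools to 22.5%, and 10% vs 50%, within the plan's explored range, pools to 30%. At about 67 patients (0.6 × 112) the 95% margin is 1.96 × √(0.225 × 0.775 / 67), about ±10 points. The DSMB review as described covers safety data, so this would be an added task.

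The main change costs wording and a short table, with no alpha and no extra patients. The downside is a less favourable stated power. Changing the primary test or adding baseline adjustment to recover power would alter the primary analysis of a running trial and is not part of this fix.

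### The sample size rests on an uncorrected chi-square test, but the primary analysis is Fisher's exact test, which has about 79% power at the 94 evaluable patients, not at least 85%

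*Protocol article*

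**What the plan says.** All references are to the protocol article.

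- **Sample size calculations and statistical analyses, the test.** Two binomial samples were simulated 999 times and "tested for a difference from zero (H0: SRD=0") "at a significance level of α=0.05". The sentence names the test as a Fisher exact chi-square test, but says that it was run "using the chisq.test() function in R without continuity correction".
- **Same section, the target.** The number of patients is chosen to "reject the null hypothesis with a statistical power of at least 85" per cent.
- **Same section, the assumptions and result.** "We assumed a success rate of 10% under placebo". The chosen scenario follows: "For an expected SR of 10% under placebo and 35% under OXT (SRD 0.25), a total of 112 patients (56 patients per group"), with 94 evaluable after 15% dropout.
- **Planned analyses.** "The primary analysis will compare success rates between groups using Fisher’s exact test", at 0.05, on the full analysis set of all randomised participants. The abstract names the same test.

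**The concern.** R's chisq.test() does not perform Fisher's exact test. Without continuity correction it returns the Pearson chi-square p-value. The label in the sample size section therefore hides the fact that the trial was sized with one test and will be analysed with another.

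The difference matters because Fisher's test conditions on the total number of successes and is conservative when success rates are low and arms are small. A number of patients that just reaches 85% under the uncorrected chi-square will fall short under Fisher. At stake is the type II error of the only confirmatory test in a rare-disease trial that would be hard to repeat. The protocol tells readers that this risk is at most 15% under its assumptions.

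**Working it through.** **Inputs**, all from the sample size section unless noted:
- success rates 0.10 (placebo) and 0.35 (oxytocin), a difference of 0.25;
- alpha 0.05, taken as two-sided because the null hypothesis is a difference of zero and chisq.test() is two-sided;
- 94 evaluable patients, and 1:1 allocation (Randomisation and blinding), so 47 per arm;
- dropout 15%.

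**Method.** For n per arm, power is the sum over all tables (a, b), with a and b from 0 to n, of Bin(a; n, 0.10) × Bin(b; n, 0.35) × 1[p(a, b) ≤ 0.05], where p(a, b) is the p-value of the test in question. At n = 47 this covers 48 × 48 tables and has no simulation error.

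**Step 1: reproduce the plan's figure.** With the uncorrected Pearson chi-square, power is 84.5% at 46 per arm and 85.4% at 47 per arm. So 94 is the smallest total with equal arms that reaches 85%. A simulation of 200,000 trials also gives 85.4%. For dropout, 47 / 0.85 = 55.3, rounded up to 56 per arm, or 112 in total. The whole chain to 94 and 112 reproduces with this test.

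**Step 2: apply the planned test at the same numbers.**

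| Test, 47 per arm | Power, 10% vs 35% | Actual type I error, 10% vs 10% |
|---|---|---|
| Pearson chi-square, uncorrected | 85.4% | 5.9% |
| Fisher's exact, two-sided | 78.6% | 1.7% |
| Boschloo's unconditional exact | 84.7% | 3.5% (maximum over all common rates 4.95%) |

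Fisher falls 85.4 − 78.6 = 6.8 points below the test used for sizing. Its type II error is 100 − 78.6 = 21.4%, against the intended 15% at most.

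**Step 3: the number Fisher needs.** Fisher's power is 84.8% at 53 per arm, 84.6% at 54, 85.5% at 55 and 86.4% at 56. It first reaches 85% at 55 per arm, or 110 evaluable. With 15% dropout, 55 / 0.85 = 64.7, rounded up to 65 per arm, or 130 recruited.

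**Step 4: the full analysis set.** The primary analysis is on all randomised patients, 56 per arm.
- If all 112 contribute outcomes at the assumed rates, Fisher's power is 86.4%.
- If 15% drop out and, as an assumption, count as failures, the rates become 0.85 × 0.10 = 0.085 and 0.85 × 0.35 = 0.2975. Fisher's power is then 77.1%.

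**Step 5: could a one-sided test explain 94?** One-sided Fisher at 0.05 already reaches 85.2% at 45 per arm, so it would have led to a smaller number.

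**The case against.** The strongest objection is that the planned analysis covers the full analysis set of 112, not 94 completers. The section on missing data expects few missing primary outcomes and would impute best and worst cases. With complete outcomes Fisher has 86.4% power. This part stands: it would be too strong to say that the planned analysis cannot reach 85%. It does not rescue the stated figure, because the protocol allows for 15% dropout and derives its power from 94 evaluable patients. Under that dropout Fisher has 78.6% on observed cases, or 77.1% if dropouts count as failures.

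A second objection is that Fisher's test is valid and conservative. That is true. No false-positive risk arises, and the defect is confined to the power claim.

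A reader might also infer two further faults, which the document does not support:
- *The trial is sized on the wrong effect*, because the text says "a moderate SRD of 20% corresponds to an NNT of five patients" while the calculation uses 25%. The 20% figure is introduced only as an example of converting a success rate difference into a number needed to treat. The section states its target of 0.25 explicitly, and nothing there says that 25% is not moderate.
- *999 simulations are too few.* The Monte Carlo standard error is √(0.85 × 0.15 / 999) = 1.1 points, about ±2.2 at 95%. Exact power for the simulated test is 85.4%, so simulation noise did not distort the number, and it is too small to account for the 6.8-point gap.

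**Conclusion.** The point holds. The sizing test is mislabelled and differs from the primary test, and the claim of at least 85% power is wrong for Fisher's exact test at the 94 evaluable patients on which the protocol sizes. The correct figure there is 78.6%. On the full analysis set it lies between about 77% and 86%, depending on how many outcomes are missing and how they are counted.

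This rests on the protocol's own rates of 10% and 35%, a two-sided 0.05 level, which is inferred, and equal arms. The figures 94 and 112 are themselves correct arithmetic for the test that was run. The error lies in attributing their power to a different test.

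**What to change.** Correct the test label in the sample size section so that it names the test actually simulated. Then take one of two routes.

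1. **Keep Fisher's exact test** and restate the power as about 79% at 94 evaluable patients, ideally with the 77% to 86% range for the full analysis set. The cost is wording and a less favourable stated power.
2. **Replace Fisher with Boschloo's unconditional exact test**, before unblinding and by amendment. It controls alpha and gives 84.7% at the same number. The power statement should then read about 85%, not at least 85%. The cost is an amendment to the primary analysis of a running trial; the Ethics and dissemination section requires ethics committee approval of substantial amendments.

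In either case, compute the figure by exact enumeration with the test that will be used. Moving the analysis to the uncorrected chi-square is the weaker way to align the two, because its actual type I error is 5.9% at a common rate of 10%.

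Neither route needs more patients. Only if the sponsor wants to hold 85% with Fisher does the number rise, to 110 evaluable and about 130 recruited.
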